## Abstract

**Background:**

Music therapy is frequently offered to individuals suffering from depression. Despite the lack of research into the effects of music therapy on this population, anecdotal evidence suggests that the results are rather promising. The aim of this study is to examine whether improvisational, psychodynamically orientated music therapy in an individual setting helps reduce symptoms of depression and improve other health-related outcomes. In particular, attention will be given to mediator agents, such as musical expression and interaction in the sessions, as well as to the explanatory potential of EEG recordings in investigating emotion related music perception of individuals with depression.

**Methods:**

85 adults (18–50 years of age) with depression (ICD-10: F 32 or F33) will be randomly assigned to an experimental or a control condition. All participants will receive standard care, but the experimental group will be offered biweekly sessions of improvisational music therapy over a period of 3 months. A blind assessor will measure outcomes before testing, after 3 months, and after 6 months.

**Discussion:**

This study aims to fill a gap in knowledge as to whether active (improvisational) music therapy applied to people with depression improves their condition. For the first time in this context, the mediating processes, such as changes in musical expression and interaction during the course of therapy, will be objectively investigated, and it is expected that the results will provide new insights into these processes. Furthermore, the findings are expected to reveal whether music related emotional experiences, as measured by EEG, can be utilized in assessing a depressive client's improvement in the therapy. The size and the comprehensiveness of the study are sufficient for generalizing its findings to clinical practice as well as to further music therapy research.

**Trial registration:**

ISRCTN84185937

## Background

Depression is the most frequent mental disorder in Finland, and its meaning as an illness from both an economic and a human suffering point of view, is among the biggest challenges of today's health-care system [1]. Prevalence of depression in Finland is estimated at 5–6,5% of the population (about 200 000 people) [2]. Lifetime prevalence is about 20% of the population. Depression is more prevalent in women (7,8%) than in men (4,1%) [3]. In addition to traditional psychiatric services, specific depression projects have been established across Finland as part of which medical professionals, mainly nurses, have been trained to assess and council people suffering from depression.

In Finnish treatment practice, medication together with psychiatric counselling is the most common combination of depression treatments. Psychotherapy is offered as well, but, according to Honkonen et al, [4] it is not often utilized. For example, of patients who retired due to depression between 1993 and1994, and between 2003 and 2004, only 9% and 11%, respectively, had received psychotherapy. This is striking given the fact that many patients suffering from severe or chronic depression do not benefit from antidepressants [5]. In particular, after the acute phase of depression, a patient should be offered the possibility of receiving cognitive and other psychological treatments [6]. Also, Honkonen et al. [4] point out that both the international and national clinical guidelines recommend that, along with an appropriate medication, the meaning of interactive treatments, such as psychotherapy, is important.

As regards medication, antidepressants such as SSRIs (selective serotonin reuptake inhibitors), MAOI (Monoamine oxidase inhibitors) and the older TCAs (tricyclic antidepressants) are mostly used [7]. However, side effects as nausea, diarrhoea, headache or anxiety are well known, and patients are therefore seeking alternative complementary treatments [8]. Music therapy has the potential to serve as an adjunct to, or facilitator of, medication, may reduce the amount of medication administered, or can even serve as a method of choice instead of medication, as demonstrated, for example, in anaesthesia [9].

That music affects the emotions is a well-known phenomena, and modern neuroscience has revealed the subcortical areas involved in emotion processing and emotional disorders [10,11]. In particular, subcortical limbic and frontal areas of the brain are thought to malfunction in depressive states, or even show morphological changes and biochemical dysfunction [12,13]. Here, music reception and interaction in music therapy seems to be a powerful non-invasive tool to stimulate brain systems and affective regulation involved in depression.

EEG studies have shown frontal alpha traces of depression. General discussion has focused on frontal alpha power asymmetry as an index of potential risk for emotion-related psychopathology, as a moderator and mediator of emotion [14], and as state and trait markers of correlated activity measures, reflecting Davidson's claim [15] that left frontal hypoactivation is a stable marker of trait vulnerability to depression and anxiety disorders [12]. As depression is found to be correlated with a hypoactivation of left brain activity [14] this may be attenuated after music therapy as earlier studies on music listening have shown [11,16-18].

After Bruscia, music therapy is defined as "a systematic process of intervention wherein the therapist helps the client to promote health, using music experiences and the relationships that develop through them..." [19]. It is often perceived as a psychotherapeutic method where musical interaction, in addition to verbal discussion, is used as means of communication and expression. The aim of music therapy is to help people with mental health problems to develop relationships, and address issues they may not be able to by using words alone [20]. Improvisational music therapy is based on active, spontaneous music making, often in a therapist-client dyad. The method typically utilizes both non-verbal and verbal expression, and the analytical (or psychodynamic) school in particular emphasizes the meaning of, and the process of dealing with, emotions and emotional processes as an essential part of the therapeutic process [21-25]. Bruscia [26] describes analytical music therapy as the use of words and symbolic music improvisations as a means of exploring the client's inner life and facilitating growth. The model was originally developed for adults with emotional or interpersonal problems. Different schools of psychotherapy have emerged and continue to develop from Freud's original work so that the title psychodynamic is currently often used instead of analytic – however, the fundamental basis of both of the models remains the same.

Several randomised controlled trials (RCTs) have previously examined the effects of music therapy for people with depression. In a recent Cochrane systematic review [27], five RCTs of adequate methodological quality were identified. Most of them compared music therapy to standard care and suggested that music therapy was accepted by people with depression and were associated with improvements in mood. However, three of the five studies were about elderly people [28-30], and one about adolescents [31]. Only one study [32] focused on people of working age (between 21 and 62 years). Music listening was a central working mode in most of the studies. Active music-making, which is often central in music therapy practice, was a central working mode in only one study [28]. Therefore, improvisational music therapy with depressed adults of working age is clearly under-researched. Furthermore, research in this area has to date suffered from methodological weaknesses such as low test power (i.e. too small sample size), inadequate randomisation procedures (e.g. lack of allocation concealment), lack of blinding, and inadequate statistical analysis and reporting.

A more thorough (mixed-effects) meta-analysis of available studies to date was conducted 2008 by Gold C, Solli H, Krüger V, Lie S in a recently submitted paper entitled 'Dose-response relationship in music therapy for people with serious mental disorders: Systematic review and meta-analysis'. The review found significant and large effects for both psychotic and non-psychotic serious mental disorders, and a strong dose-response relationship. Findings suggested that music therapy helps patients to improve general symptoms, depression and anxiety symptoms, and level of functioning, and provided estimates of the effect per session, which can be used in power calculations for future studies. Overall, the review supported the conclusion that music therapy is an effective treatment for depression, and suggested that future research should, besides improving methodological quality, specifically address the working modes and the underlying theories of music therapy approaches.

The aims of the study will be:

1. To examine if improvisational music therapy in addition to standard care helps reduce levels of depressive symptoms (primary outcome) compared to standard care only.

2. To examine with psychiatric tests if music therapy reduces general symptoms, alexithymia, functioning, and quality of life in these patients compared to standard care.

3. To examine if music therapy diminishes frontal asymmetry in rest EEG (as a proxy/indicator of clinical changes in depression level)

4. Provided that significant effects are found: to examine if clinical change is mediated by observable and measurable changes in music (i.e. improvisations recorded in therapy) and its elements, in specific musical features, and in the interaction between the client and the therapist.

5. Provided that significant effects are found: to examine if these effects are mediated by changes in music perception (as measured in topographic EEG focusing on changes in frontal and limbic responses; additionally as expressed in self-ratings).

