### Experimental group

#### a) Music therapy

Clients of the experimental group will participate in psychodynamic improvisational music therapy in an individual setting. Music therapy will be conducted twice a week, each session lasting 60 minutes. A total of 20 sessions will be offered, and therapists should aim to complete at least 16 sessions. However, patients with fewer sessions will not be excluded from data analysis (intention-to-treat principle). Active engagement during the therapy process is required for up to 3 months.

The music therapy to be offered is based on the ideas and principles of improvisational music therapy [21,22], and the application of the ideas of Priestley's [36] analytical music therapy. The practical application of the clinical improvisation method has been developed during the training of therapists involved in this research project at JYU Music Therapy Clinic for Research and Training. The basic principle of the intervention is to encourage and engage a client in expressive musical interaction. The starting point for improvisation may be either free or referential. The shared experience is discussed, and the therapeutic process is based on the mutual construction of meaning of emerging thoughts, images, emotional content, and expressive qualities as reflected and understood within the context of the psychodynamic framework.

All improvisations are recorded to computer, and they may be listened to during the same session or afterwards for further processing and discussion. Other than this, no music listening is used as a method; the main focus is on active expressive music making with verbal processing of the experience. Instrumentation is restricted to the use of mallet midi controllers, midi-percussion and modified Djembe-drums (to meet the special needs of data collection in this research project). Every therapy session will be video recorded for data collection and supervision.

The music therapy clinicians who have committed to the study have professional training in music therapy. In addition, they have been specifically trained in the clinical method and it's theoretical basis. This latter training lasted over one year, and was focused on theoretical concepts, the application of clinical improvisation, and process handling issues (building and maintaining a therapeutic relationship, transference & counter-transference, choosing appropriate interventions, verbal processing, gaining insight, etc.).

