### Control group

#### Standard care

Patients will receive treatment as usual during the study period. As in the experimental group, standard care may consist of medication (antidepressants) and psychiatric counselling, which will be monitored in the same way as described above for the experimental group.

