### Sample size

A power calculation was carried out for the primary outcome (depressive symptoms) and secondary outcomes (general symptoms, functioning). The following assumptions were used in the calculation:

- Number of sessions: The number of sessions is an important predictor of the effect size of music therapy and should therefore be included in a power calculation (Gold C et al, Dose-response relationship in music therapy for people with serious mental disorders: Systematic review and meta-analysis, Unpublished). The target number of sessions in this study is 20. As a conservative estimate, it is assumed that participants will attend at least 15 sessions on average.

- Effect sizes: According to the meta-regression models developed (Gold et al, Dose-response relationship in music therapy for people with serious mental disorders: Systematic review and meta-analysis, Unpublished)the expected effect sizes (standardised mean differences) of 15 sessions of music therapy, compared to standard care, for patients with mental disorders, are as follows: depressive symptoms, .75 (a large effect); functioning, .42 (medium effect).

- Number of subjects to be included: With the funding and time frame available, the feasible number of subjects to be included in the experiment will be 85. Of these, it is estimated that up to 10% may drop out during the study, resulting in a total of 76 cases with available data at posttest.

Based on these assumptions, the power of a t-test was calculated using R package pwr [37]. With the effect sizes derived above, alpha = 0.05, and 31 and 45 complete cases in each of the two groups, the power will be 88% for depressive symptoms and 43% for functioning. (This is a conservative estimate because it does not take into account pretest scores.) As depression will be the primary outcome, the intended sample size will be sufficient for an exploratory trial.

After inclusion in the study and pretest assessment, the participants will be allocated to conditions using a computerised randomisation procedure. This will be done by the external expert that has no direct contact with the patients in order to conceal the allocation from the involved clinicians. An overview of the study design is shown in Figure 1.

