### Secondary outcomes specifically linked to the assumed mechanisms of music therapy

#### Music analysis

All the improvisations created in the therapy sessions will be recorded either as MIDI-data (mallet midi-controllers and midi-percussion) or as digital audio (Djembe drums). For the analysis of MIDI-data, a computational method called MTTB (Music Therapy Toolbox), specifically developed for the analysis of music therapy improvisations in MIDI-format, will be employed. The MTTB-method enables the automatic extraction of various musical features from an improvisation, as well as the examination of certain aspects of the therapist-client interaction. The method has been successfully utilized in the analysis of clinical improvisations by people with mental retardation [54,55]. For the analysis of digital audio data, a computational method called MIR (Music Information Retrieval) will be employed [56]. Like the MTTB, MIR also enables the extraction of specific musical features from the music, and the examination of musical interaction between therapist and client. MIR has not been utilized in a clinical context before.

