### EEG

EEG measurement will be conducted based on the findings of earlier research on depression. Because of it's time-locked correlations, EEG has become the measure of choice for music and brain research; brain imaging techniques that provide distinct spatial information (such as fMRI and PET), for example, lack time and event-related correlations [58,59].

Depression has been found to be correlated with a hypoactivation of left brain activity [14], and this may be improved after treatment [11,16]. Secondly, a more distinct and variable spectral EEG pattern according to personality [60], and specific reactions of theta variables [61] in the treatment and control group, are expected as mediators of change.

EEG research recordings (pretest directly after inclusion/before randomization, post-test 3 months after randomisation) and its corresponding patient data of the clinical groups will be monitored by a clinical neurologist. Analysis of the EEG will focus on topographic distribution of spectral power and percentage of EEG frequencies.

All subjects will listen to two sets of stimuli:

1.) Ordered, but randomly allocated sets of short pieces of instrumental music characterising 5 basic emotions (tenderness, anger, fear, sadness, happiness).

2.) A randomised order of short pieces of instrumental music comprising excerpts of film soundtracks previously rated and categorised according to the emotional dimensions of valence, tension, and energy [Eerola T: **Mapping Musical Features to Perceived Emotions sing Partial Least Squares Regression [Submitted]**. In *The 10th International Conference on Music Perception and Cognition*. Sapporo, Japan: The Center for Research and Development in Higher Education, Hokkaido University, Sapporo, Japan; 2008].

The EEG data will be correlated with the results of the behavioural test for emotional qualities of music (see below), which will contain the same two data sets. This test will be administered after the EEG investigation. To avoid repetition, the excerpts in both sets will be presented in another random order.

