### Statistical analyses

Results will be analysed on an intention-to-treat basis, using general linear mixed-effects models and effect sizes with 95% confidence intervals. Mediator processes will be examined using structural equation modelling.

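### Aim 4 asks about mediation through in-session improvisation, which is recorded only in the music therapy arm, so mediation of the randomised effect by that route is not identified

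*Protocol article*

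**What the plan says.** The list of aims at the end of the Background section gives aim 4, conditional on significant effects being found, as "to examine if clinical change is mediated by observable and measurable changes in music (i.e. improvisations recorded in therapy) and its elements". The same sentence adds specific musical features and the interaction between client and therapist. The Discussion paragraph of the Abstract says that "the mediating processes, such as changes in musical expression and interaction during the course of therapy, will be objectively investigated".

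The source of these measures is given under Music analysis: "All the improvisations created in the therapy sessions will be recorded either as MIDI-data", or as digital audio for the drums. Under Experimental group, Music therapy: "Clients of the experimental group will participate in psychodynamic improvisational music therapy in an individual setting". Under Control group, Standard care: "Patients will receive treatment as usual during the study period". No improvisation task is described for controls at any time point.

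The method is one sentence under Statistical analyses: "Mediator processes will be examined using structural equation modelling".

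Aim 5 rests on other measures. The EEG section says "All subjects will listen to two sets of stimuli", and the behavioural music test is planned for participants before randomisation and at 3 and 6 months.

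**The concern.** To say that a variable mediates a treatment effect is to say that randomisation shifts the variable and that the variable in turn shifts the outcome. The first step compares the variable between arms. Here the variable is the patient's playing in therapy, which is part of the experimental treatment and does not exist for controls. The comparison cannot be made.

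What can be estimated is whether, among treated patients, those whose playing changed more also improved more. Randomisation gives that association no protection. Patients who feel better may play differently. Medication may alter both playing and the MADRS (the primary outcome); the main Discussion section itself notes that medication may be adjusted during the trial and that this matters when expressivity is analysed.

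Mechanism is prominent in this article. If the aim and the Abstract keep the language of mediation, a one-arm association could be read as the pathway of a randomised effect.

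**Working it through.** **1. The plan's own figures.** The Sample size section assumes "alpha = 0.05, and 31 and 45 complete cases in each of the two groups", with standardised differences of 0.75 (depressive symptoms) and 0.42 (functioning), and states power of 88% and 43%. For a two-sided two-sample t-test with 31 + 45 − 2 = 74 degrees of freedom, the noncentrality is d × √(31 × 45 / 76) = d × 4.284, that is 3.21 and 1.80. Power is 88.7% and 42.7%, so the stated figures reproduce. Total complete cases: 85 × 0.9 = 76.5, stated as 76. The article gives no figure for the mediation analysis.

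**2. Which arm has which measure.**

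| Measure | Music therapy arm | Control arm |
|---|---|---|
| MADRS | yes | yes |
| EEG with music, music-emotion ratings (aim 5) | yes | yes |
| Musical features and interaction in sessions (aim 4) | yes | none |

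**3. Identification.** Let X be arm, M the musical measure and Y the outcome. The usual decomposition is:

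- a = mean of M in the treated arm − mean of M in controls
- Y = constant + c′X + bM
- indirect effect = a × b; direct effect = c′; total effect = ab + c′

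The control mean of M is never observed, so a is unknown. If the analyst fills in a constant k for every control, M has no variation among controls and b is determined by the treated arm alone. Then a = (treated mean of M) − k, and c′ = total − ab. Both parts depend on k, and no data bear on k.

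**4. Illustration.** One simulated data set, with every parameter assumed: 31 treated and 45 controls (this assignment is also assumed), treated M with mean 0.5 and SD 1, treated Y with mean 0.75 and slope 0.4 on M, control Y with mean 0, residual SD 1. The fitted slope b was 0.483 and the total effect 0.736 throughout.

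| k | a | indirect (ab) | direct (c′) |
|---|---|---|---|
| −1 | 1.504 | 0.727 | 0.009 |
| −0.5 | 1.004 | 0.485 | 0.251 |
| 0 | 0.504 | 0.244 | 0.492 |
| 0.5 | 0.004 | 0.002 | 0.734 |
| 1 | −0.496 | −0.240 | 0.976 |

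With the same outcomes, the effect appears almost wholly mediated, not mediated, or mediated in the opposite direction, according to k. Coding absent playing as zero is one row of this table and has no special standing.

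**5. Precision of what remains.** This is context only, because non-identification does not depend on sample size. For a single within-arm correlation (Fisher z, two-sided 0.05), 80% power needs r = tanh[(1.960 + 0.842)/√(n − 3)], which is 0.485 for n = 31 and 0.407 for n = 45. At an assumed r of 0.3, a value not in the article, power is 37% or 52%. An observed r of 0.3 with n = 31 would have a 95% confidence interval of −0.06 to 0.59.

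**The case against.** The best defence is that aim 4 does not claim what a two-arm mediation model would estimate. Aim 4 speaks of clinical change, whereas aim 5 speaks of the effects found; only aim 5 refers plainly to the between-arm difference. Read this way, aim 4 is a process question among treated clients. Structural equation modelling also covers single-group and repeated-measures models, and up to 20 recorded sessions would allow time-ordered analysis. The choice of model is a detail that an article may leave to a fuller document. The main Discussion section asks how musical expression and interaction both reflect and contribute to recovery, so the authors have both directions in view. Aim 4 is also conditional, and its measures are listed as secondary outcomes.

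Much of this stands. The within-arm reading is possible, the analysis it implies is feasible, and the single sentence on structural equation modelling does not commit the trial to a two-arm decomposition. Two things remain. First, aim 4 opens only if significant effects are found, which sets it up to explain those effects, and the Abstract calls the same measures mediating processes. Secondly, no model and no unseen analysis plan can supply a measure that the design does not collect in controls. Even on the favourable reading, the result is a non-randomised association, and the word mediated overstates it.

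A reader might go further and infer that the trial cannot study mediation of its effect at all. The article does not support that: the aim 5 measures are planned in both arms, so the path from arm to mediator can be estimated there. Nor does the article say that a within-arm association will be reported as the randomised pathway. That is a risk created by the wording.

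**Conclusion.** The point holds for the in-session measures of aim 4 only. Mediation of the randomised effect through in-session improvisation is not identified, because the mediator is absent by design in the whole control arm. The estimable quantity is an association within the music therapy arm, on 31 or 45 of the planned 76 complete cases, open to reverse causation and confounding.

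The conclusion rests on one reading of the article: that controls have no recorded improvisation. Nothing in the text suggests otherwise. It does not depend on the simulation or on the assumed correlation of 0.3; those show how arbitrary the split would be and how little one arm can resolve.

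Severity is moderate. A reader might infer that the main result is compromised. It is not: the primary outcome, the sample size and the primary analysis do not involve these measures. What changes is what the trial may conclude about mechanism.

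**What to change.** - Reword aim 4 as an exploratory process-outcome association within the music therapy arm.
- Replace the mediation terms for in-session measures in aim 4 and in the Abstract's Discussion paragraph.
- In Statistical analyses, limit structural equation mediation of the treatment effect to measures taken in both arms (EEG and music-emotion ratings).
- For the within-arm analysis, use process change that precedes the outcome and adjust for pretest MADRS. One option among several is early-to-mid-therapy change in a short fixed list of musical features as a predictor of 3-month MADRS. This reduces reverse causation but leaves the association non-randomised, so medication changes should be considered as a confounder.

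The cost is the rewording of an aim and two sentences. No new data are needed, and the mechanistic claim becomes weaker. If the authors want to keep a mediation claim for musical expression, they would need a standard improvisation measure in both arms before and after treatment. That is new data collection, and it would measure playing in a test setting rather than in therapy.
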